## Methods and design

### Trial design

This study is a single-center, prospective, randomized, triple-blind trial to compare the safety and efficacy of two sclerosing agents (0.2% polidocanol plus 70% hypertonic glucose versus 75% hypertonic glucose) in women over 60 days.

### Patient enrollment and randomization

A convenience sample of patients undergoing treatment for mild varicose veins will be employed. Patient information will be entered into an electronic database, and participants will later be contacted to attend an outpatient evaluation. In the first evaluation, patients who have a reticular vein measuring at least 10 cm long in the outer-side of the leg and/or thigh will be invited to join the study. The sample size was estimated to be 96 treated limbs (see “Statistical analyses”). All subjects will be informed of study risks and will be required to sign an informed consent form approved by the institutional review board. The random allocation schedule will be generated using the computer program Stat Trek (http://stattrek.com/Tables/Random.aspx).

Two groups will be established for the treatment of reticular veins, including either 0.2% polidocanol diluted in 70% glucose or 75% glucose alone. A trained nurse will store all data and remain in charge of arrangements, such as preparing the solutions used in the treatments, throughout the duration of the study. Solutions will be prepared in a specific room (different from the office) using sterile 10 mL syringes. Syringes will be identified according to a random number given to each patient.

### Ethics

This trial is being conducted in accordance with the principles of Helsinki’s Declaration, ISO14155 and Good Clinical Practices guidelines. The Research Ethics Committee of the Botucatu Medical School, from the Paulista State University, São Paulo State, Brazil, approved this trial, which was registered under protocol number CEP4127-2012. A written informed consent was obtained from all subjects before enrollment. Subjects can withdraw from this trial whenever at their own discretion, with no prejudice. The *ClinicalTrials.gov* identifier for this trial is NCT02054325 and was obtained on February 3, 2014.

### Clinical and pre-treatment measures

Patients will be included if they present one or more reticular veins with a minimal length of 10 cm, and no edema or palpable tortuosity. A duplex ultrasonography will then be performed prior to treatment. Clinical data, such as comorbidities, demographic features, and other relevant information, will be collected for later analysis. All excluded patients will be referred for other clinical follow-up techniques at the institution.

### Inclusion and exclusion criteria

#### Inclusion criteria

Women, having one or more reticular veins measuring at least 10 cm long on the outer side of the leg and/or thigh with a clinical classification of C1 CEAP [18] (which means absence of varicose veins), aged between 18 and 69 years, who agree to the terms of the research, sign the free consent form, available to make the required appointments necessary for follow-up, consent to avoid pregnancy for at least three months after the treatment, and do not use anticoagulant drugs (Additional file 1).

#### Exclusion criteria

Males, females with CEAP 2 to 6 [18], low mobility, peripheral arterial disease, known allergy history to the drugs used in this study (glucose and polidocanol), presence of dermatitis in the lower limbs and presence of comorbidities (such as diabetes mellitus, heart failure, respiratory failure, uncontrolled hypertension, hypothyroidism or hyperthyroidism), pregnancy, breastfeeding, pulmonary hypertension, prior deep venous thrombosis (DVT), familiar history of DVT, known hypercoagulable states or thrombophilia, asthma, migraine, or anyone that does not agree with any of the research terms (Additional file 1).

### Treatment area

To define the treatment area, on the outer side of the lower limbs (thigh and leg) and using the fibular head projection as an anatomical reference point, a longitudinal imaginary line measuring 25 cm (up) and 15 cm (down) will be drawn using the fibular head as a starting point. Two additional lines will be drawn parallel to the first one, with one marked at 7.5 cm anterior and the other at 7.5 cm posterior, which define the limited area for treatment (600 cm^2^; Additional file 2). In this area, one or two reticular veins, measuring from 10 cm to 20 cm in total length, will be treated with a minimum of 10, and a maximum of 30, punctures and with 5 mL as the maximum volume of medication over the treatment duration. Each puncture will not exceed 0.3 mL of volume.

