**Methods/design:**

Inclusion criteria are women between 18 and 69 years old with at least 10 cm long reticular veins in the lower limbs, on the outer side of the leg/thigh. Patients with CEAP 2 to 6, or with allergies, pregnancy, performing breastfeeding, or with any dermatologic or clinical problems will be excluded. Patients with venous ultrasound mapping showing involvement of saphenous trunks and/or a deep venous system will also be excluded. Patients will be randomized into two groups, one receiving 75% pure glucose and the other group receiving 0.2% polidocanol diluted in 70% glucose. Just one limb and one session per patient will be performed. The sclerosing agent volume will not exceed 5 mL. Clinical follow-up will include visits on days 7 and 60, always with photographic documentation.

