### Treatment (D0)

After the photographs are taken, the two groups will be treated similarly to eliminate all the reticular veins in the area of the selected lower limb. All procedures will be performed by the same physician. A rigorous conventional sclerotherapy technique will be followed, consisting of careful injections to prevent leakage of fluid into the subcutaneous tissue. The procedure will be performed until veins become undetectable. The maximum volume allowed per puncture will not exceed 1 mL. A 3 mL luer-lok plastic syringe BD® will be used with a 13 × 4 Terumo® needle (27 G1/2). Bandages will be performed with a cotton ball (approximately 0.3 cm in diameter) attached to a square piece of plaster tape (measuring approximately 2 × 3 cm) right after the completion of the procedure to stop backflow. Before discharge, the target area will be submitted to elastic compression using a 1.5 m long elastic band (Atadress®) for one day [19].

All treatment data will be gathered, including the minimal volume of solution necessary for the whole disappearance of all the reticular veins in the target area, number of punctures, location of the target area, possible allergic reactions, and existence of minimum varicose veins in the target area. Additionally, a form will be given to the patient to fill out to report discomfort or pain triggered by the treatment (Additional file 3). Patients will be given careful oral and written instructions on how to proceed after treatment (Additional file 4). All patients will receive one tube of cream containing 0.5% sodium heparin to treat any initial blemishes, to be used twice per day for two weeks.

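### The protocol article limits the volume per puncture to 0.3 mL in one section and to 1 mL in another, and does not say how the end rule relates to the 5 mL cap

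*Protocol article*

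**What the plan says.** Two sections of the protocol article set rules for the same procedure. The abstract (Methods/design) confirms that each patient has one limb treated in one session.

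- **Treatment area, volume per puncture:** "Each puncture will not exceed 0.3 mL of volume".
- **Treatment (D0), volume per puncture:** "The maximum volume allowed per puncture will not exceed 1 mL".
- **Treatment area, counts and total:** "a minimum of 10, and a maximum of 30, punctures and with 5 mL as the maximum volume of medication over the treatment duration". The abstract repeats the total: "The sclerosing agent volume will not exceed 5 mL".
- **Treatment (D0), when to stop:** "The procedure will be performed until veins become undetectable".
- **Extent of treatment:** Treatment area speaks of "one or two reticular veins, measuring from 10 cm to 20 cm in total length". Treatment (D0) says that "the two groups will be treated similarly to eliminate all the reticular veins in the area of the selected lower limb".

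Treatment (D0) also states that one physician performs all procedures, and that solution volume and number of punctures are among the data collected. Volume per individual puncture is not in that list.

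**The concern.** A limit on an injected study drug should have one value. Here it has two, in sections that an operator or monitor would both consult, and neither refers to the other. An injection between 0.3 mL and 1 mL is a deviation under one section and permitted under the other. At low puncture counts the choice of limit also changes the largest total that a patient may receive. The trial has a safety hypothesis (non-inferiority of the polidocanol mixture), so the report will need to say whether the volume rules were followed.

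A second, smaller point concerns the end of the procedure. One section pursues the disappearance of all reticular veins in the area. The other caps volume and punctures and speaks of one or two veins. If veins are still visible when a cap is reached, the text does not say what follows. The primary score is based on the length of vein remaining in the target area at D60. Veins left untreated because a cap was reached would therefore count in the same way as veins that were injected and failed to close.

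**Working it through.** **Inputs.** Per-puncture limits of 0.3 mL (Treatment area) and 1 mL (Treatment (D0)); 10 to 30 punctures and at most 5 mL in total (Treatment area; the total also in the abstract).

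**Step 1: size of the contradiction.** 1 / 0.3 = 3.3. Both figures are maxima for the same act in the same session, and no wording confines either to a particular vein, syringe or phase.

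**Step 2: largest permitted total.** For *n* punctures, a per-puncture limit *v* and the 5 mL cap, the largest permitted total is the smaller of *n* × *v* and 5 mL. With *v* = 1 mL and at least 10 punctures, *n* × *v* is at least 10 mL, so the cap always governs.

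| Punctures | 0.3 × n (mL) | Largest total, 0.3 mL limit | Largest total, 1 mL limit | Gap |
|---|---|---|---|---|
| 10 | 3.0 | 3.0 mL | 5.0 mL | 2.0 mL |
| 16 | 4.8 | 4.8 mL | 5.0 mL | 0.2 mL |
| 17 | 5.1 | 5.0 mL | 5.0 mL | 0 |
| 30 | 9.0 | 5.0 mL | 5.0 mL | 0 |

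At 10 punctures the 1 mL limit permits 5.0 / 3.0 = 1.67 times the total, that is 67% more. From 17 punctures on, the cap governs under either limit and the permitted totals are the same.

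**Step 3: a worked case.** Take 4 mL in 10 equal injections: 4 / 10 = 0.4 mL each. The count and the total comply with every section. The volume per puncture breaches Treatment area (0.4 > 0.3) and complies with Treatment (D0) (0.4 < 1).

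**Step 4: what the recorded data can show.** Total volume divided by number of punctures gives only a mean. A mean above 0.3 mL proves that at least one injection exceeded 0.3 mL. Within the cap this can happen only with 10 to 16 punctures, because 5 / 16 = 0.31 mL but 5 / 17 = 0.294 mL. A mean can never reveal a breach of 1 mL within the cap, because 5 / 10 = 0.5 mL is the largest mean possible. So the limit that was applied cannot in general be recovered from the recorded totals.

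**Step 5: are the puncture range and the cap compatible?** At the cap, the mean per puncture is 5 / 10 = 0.5 mL for 10 punctures and 5 / 30 = 0.167 mL for 30. Ten punctures at up to 0.3 mL use at most 3.0 mL, and 30 punctures fit within 5 mL at a mean of 0.167 mL. Every count from 10 to 30 can therefore satisfy the cap together with either per-puncture limit.

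**Step 6: sample size.** The stated power of more than 80% (48 per arm, difference 0.9, SD 1.5, alpha 0.05, taken as two-sided because the article does not say) reproduces. The standardised difference is 0.9 / 1.5 = 0.6, and 0.6 × √(48/2) − 1.96 = 0.98, which gives 83.6% by the normal approximation; the t-test gives 82.9%. Injection volume does not enter this calculation.

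**Step 7: end rule against cap.** The two meet only in a patient whose veins are still visible at 5 mL or at 30 punctures. In every other patient both rules can be followed. The article does not say how often this is expected.

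**The case against.** The strongest case on the other side is that the exposure which matters is well controlled. The total cap is the same in both places that state one. The same text applies to both arms, one physician treats everyone, and syringes are prepared in another room and coded by random number. Exposure is titrated to effect by design, and count and total can be checked against unambiguous limits. On this view the discrepancy is a slip of drafting in a condensed article, and the ordinary reading of the end rule is to pursue it within the ceiling.

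Most of this stands. A reader might infer that the puncture counts contradict the cap, because 30 × 0.3 = 9 mL and 10 × 1 = 10 mL both exceed 5 mL. They do not. All the figures are simultaneous maxima, so the products show only that not every puncture can use its full allowance; the 10 mL product is a consequence of the 0.3/1 mL conflict and not a separate error. A reader might also infer that the exposure under comparison is left open, or that the arms would be treated differently. The documents do not support that: the total is capped consistently and the ambiguity is common to both arms. If one agent needed more volume, reaching the cap could differ by arm, but nothing in the article shows this.

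The Background links serious polidocanol events to miscalculated dosages. It says nothing about volume per puncture, so it lends general weight to clear dosing text and no more. Nor can it be said that the 25 patients reported as treated were treated under contradictory instructions, because the operating protocol is not shown.

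Condensation does not explain the contradiction away. Nothing has been left out here; two incompatible values are printed.

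**Conclusion.** The per-puncture limit is contradictory as written: 0.3 mL against 1 mL, a 3.3-fold difference, for the same session. The consequence is bounded. The permitted total differs only at 10 to 16 punctures, by 2.0 mL at 10 and falling to 0.2 mL at 16, and adherence to this one limit cannot be assessed. Adherence to the puncture range and to the 5 mL total can be. No bias between arms and no change in power or sample size is shown.

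The relation between the end rule and the cap is a secondary point. It is an unaddressed case, not a contradiction, and its importance depends on how many patients reach a cap with veins still visible, which the article does not give. Treatment data defined by complete disappearance of the veins would be cut off at 5 mL in those patients, but that volume is neither the primary endpoint nor a listed secondary one.

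The conclusion rests on reading both sections as applying to all injections in the single session, which is the only reading that the text offers. It takes no position on which limit is right.

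**What to change.** 1. Reconcile Treatment area and Treatment (D0) to a single per-puncture limit. The clinical team must decide the value.
2. State how the end rule relates to the volume and puncture caps, and whether treatment covers one or two veins or all reticular veins in the area. These are also clinical decisions; the text needs only to give one answer.
3. For patients already treated (25 are reported, none of whom had reached D60), document which per-puncture limit was applied. As shown above, the recorded totals cannot be relied on to reveal it.
4. Flag in the data set each patient who reached 5 mL or 30 punctures, and tabulate the flag by arm. It follows from volume and puncture data already recorded. A note of whether veins were still visible at that moment would make it more useful, since volume and count alone do not show this.

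The cost is a protocol clarification to the ethics committee, a short file note on past practice and one derived variable. Recruitment was still open when the article was written, so the clarification could take effect for the remaining patients. No sample size or analysis needs to change.

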### Photographic registry

Photos of patients will be taken to register the early and late results of the treatment area (pre-treatment). A high definition camera (D7000 Nikon™ Lens: AF-S Nikkor™ 18–105 mm 1:3.5-5.6G) will be used to obtain these pictures. The target area, described above, will be photographed before treatment (pretreatment) to prevent a possible time bias related to the patient’s illness. Patients will be placed in a standing position on a platform with the target area facing the camera, which will be placed 1.0 m away. A high-definition standardized scale (attached to the platform) will be used to perform all measurements. The room will be arranged with ideal lighting.

Pictures will be stored in files for later analysis using ImageJ™ software. Each photo will be identified with code numbers (according to the randomized number of the protocol), matching the moment of the study (Day 0 (D0) and D60). ImageJ software will be used to measure the length of the treated veins by turning pixels into centimeters using a 2 cm line drawn upon the standardized scale. Measurements will be taken from the photos before and after the study.

### Treatment (D0)

After the photographs are taken, the two groups will be treated similarly to eliminate all the reticular veins in the area of the selected lower limb. All procedures will be performed by the same physician. A rigorous conventional sclerotherapy technique will be followed, consisting of careful injections to prevent leakage of fluid into the subcutaneous tissue. The procedure will be performed until veins become undetectable. The maximum volume allowed per puncture will not exceed 1 mL. A 3 mL luer-lok plastic syringe BD® will be used with a 13 × 4 Terumo® needle (27 G1/2). Bandages will be performed with a cotton ball (approximately 0.3 cm in diameter) attached to a square piece of plaster tape (measuring approximately 2 × 3 cm) right after the completion of the procedure to stop backflow. Before discharge, the target area will be submitted to elastic compression using a 1.5 m long elastic band (Atadress®) for one day [19].

All treatment data will be gathered, including the minimal volume of solution necessary for the whole disappearance of all the reticular veins in the target area, number of punctures, location of the target area, possible allergic reactions, and existence of minimum varicose veins in the target area. Additionally, a form will be given to the patient to fill out to report discomfort or pain triggered by the treatment (Additional file 3). Patients will be given careful oral and written instructions on how to proceed after treatment (Additional file 4). All patients will receive one tube of cream containing 0.5% sodium heparin to treat any initial blemishes, to be used twice per day for two weeks.

### Post-treatment (D7)

On approximately the seventh day, a new clinical evaluation will be performed (7 ± 2 days after the treatment session; D7). At this appointment, early results of the treatment will be evaluated, focusing on adverse events (minor or major) such as allergies, edema, respiratory complaints, syncope, scotoma, suspected DVT, and phlebitis. If identified, these adverse events will be recorded. Should phlebitis occur, it will be released with microneedle punctures (13 × 4.5 BD®) and gentle compression. An image from the target area will be recorded and placed at the same position as described above.

### Post-procedure (D60)

After 60 ± 15 days, the last clinical evaluation will be performed. Efficacy issues will be recorded and a new photo register (from the target area) will be performed, according to the procedures described above. In addition, any new adverse event that has been reported for the patient or noticed during the physical examination (allergies, edema, respiratory complaints, syncope, scotoma, suspected DVT, phlebitis, ulceration) will be registered. In case of phlebitis, treatment will be the same as described above.

### Outcomes

#### Primary endpoint – efficacy

Analysis of the primary endpoint (efficacy) will be based on the ability of each treatment to promote the disappearance of the reticular veins after 60 days of treatment (D60). Efficacy will be scored according to commonly used visual aesthetic aspects [2]. Photo analysis will be used to evaluate efficacy (from D0 to D60), which will be performed by two external physicians (both vascular surgeons) who are blinded to treatment modality. According to the image, these judges will assign scores for each patient as follows: 5 (excellent – complete healing at the target area); 4 (very good – presence of up to 1 cm of non-healed veins in length at the target area); 3 (good – presence of 1 cm to 3 cm of non-healed veins in length at the target area); 2 (fair – presence of 3 cm to 5 cm of non-healed veins in length at the target area), 1 (bad – presence of 5 cm to 9 cm of non-healed veins in length at the target area), and 0 (unsuccessful – presence of more than 9 cm of non-healed veins in length at the target area) (Additional file 5). Prior to these analyses, both judges will be trained with 10 random patients to standardize the methods of measurement.

If there are conflicting results in the scores assigned by the two judges (divergence in scores up to 1 point), a third previously trained judge will be assigned to independently score that image, and the final score will be the average of the scores from the three judges. However, if there are conflicting results in the scores assigned by the two judges (divergence in scores greater than 2 points), a conference among the two judges with a third previously trained judge will be arranged to define a consensus on the final score. All these procedures will be carried out in a blind manner.

#### Secondary endpoint – safety

Any type of adverse event (major or minor) that arises through the period of the study (D0 to D60) will be tracked. Reports, such as pain due to the procedure (discomfort reported by the patient, caused by needle punctures, and/or agent indwell), will be evaluated using the “Patient Satisfaction Questionnaire”. Adverse events that will be directly analyzed at the secondary endpoint (Additional file 3) are stains (limited to the target area), hematomas (limited to the target area), edema, and phlebitis (limited to the target limb). DVT is a severe, but unusual, complication with few existing reports documenting its effects [15]. However, this complication will also be recorded if it occurs. All of these data will be collected during medical visits (D0 to D60).

The photos taken at the end of the study (D60) will be used to evaluate irreversible skin changes such as hyperpigmentation. Two external physicians (both vascular surgeons), blinded to which modality of treatment was carried out, will score the changes as follows: 5 (excellent – no visible hyperpigmentation at the target area); 4 (very good – presence of only one point of hyperpigmentation up to 1 cm in length at the target area); 3 (good – presence of 2 to 3 points of hyperpigmentation up to 1 cm in length at the target area); 2 (fair – presence of 4 to 5 points of hyperpigmentation up to 1 cm in length, or one hyperchromatic line, up to 5 cm in length, at the target area); 1 (bad – presence of more than 5 points of hyperpigmentation up to 1 cm in length, or one hyperchromatic line, with more than 5 cm and less than 9 cm in length, at the target area); and 0 (unsuccessful – presence of a hyperchromatic line larger than 9 cm in length, or the total extension of the vein presenting hyperpigmentation, at the target area) (Additional file 6). Any conflicting results in the scores assigned by the two judges will be handled as described in the “Primary endpoint” section above.

Other data will be gathered in the analysis such as demographic data, skin color, and skin changes at the target area (pain, phlebitis, stains). Major adverse events, such as deep venous thrombosis, will also be reported throughout the study.

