## Background

According to the definition of the clinical, etiological, anatomical, and pathological classification (CEAP), the reticular veins are included in the C1 class and are mainly associated with aesthetic complaints. Several invasive techniques are commonly used for treatment, including mini phlebectomy, laser ablation, and radiofrequency ablation. However, a wide range of sclerosing agents may serve as minimally invasive alternatives, promoting chemical sclerosis of the vein wall. Reticular veins have a diameter no greater than 3 mm and are straight, bluish, and located in the subcutaneous tissue of the lower limbs [1]. They have the same complex etiology of all types of primary venous insufficiency such as hormonal issues, family history, and standing position [2, 3]. However, despite its common occurrence, the condition remains poorly understood [4]. Sclerotherapy is the preferred treatment for some patients because of its simplicity and reproducibility [5, 6], and consists of an intraluminal sclerosing agent application to trigger endothelial injury, with subsequent luminal occlusion of these segments. Many agents, such as hypertonic saline and hypertonic glucose as hyperosmolar sclerosing agents, as well as ethamolin® and polidocanol as detergent agents [5, 7], are known to be effective. Hypertonic osmotic solutions cause dehydration and destruction of endothelial cells. Hypertonic dextrose (or glucose) and sodium tetradecyl sulfate are commonly used due to their low cost and safety [8–10]. Conversely, polidocanol acts as a detergent on vein wall lipids, destroying the cellular cement and causing endothelial maceration; this process effectively occludes the vein [11–14]. Due to its efficacy and manipulability, the use of polidocanol is quite common throughout the world. Usually, it is mixed with a wide variety of diluents, such as distilled water, air, or hypertonic glucose. However, some collateral damage can occur from these mixtures, including necrosis, hyperpigmentation stains, allergic reactions, and systemic disorders. Chest pain, cough, anaphylaxis, scotoma, and gas embolization are unusual, but serious adverse events have already been reported in other studies due to this agent, although these issues are commonly related to miscalculated dosages [15–17].

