### Hypothesis

We hypothesize that 0.2% polidocanol plus 70% hypertonic glucose is superior to 75% hypertonic glucose alone in promoting the disappearance of reticular veins of the lower limbs. Moreover, we hypothesize that 0.2% polidocanol plus 70% hypertonic glucose is not inferior to 75% hypertonic glucose in terms of safety.

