### Expected adverse effects

Both selected study drugs (75% hypertonic glucose and 0.2% polidocanol) are widely used as sclerosing agents in aesthetic venous procedures. There are a few reports of 75% hypertonic glucose usage resulting in major complications. However, polidocanol is associated with some reports of adverse events such as gas embolism and deep venous thrombosis. Pain, local edema, stains, phlebitis, and ulcers are minor adverse events related to these agents. If any other relevant effects occur, they will be reported to the Ethics Committee.

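### The overall safety non-inferiority hypothesis is not supported: the directly analysed adverse events omit the collected systemic events and ulceration, there is no margin, and 48 per arm says little about rare events.

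*Protocol article*

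**What the plan says.** All references are to the Protocol article.

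- **Hypothesis.** The polidocanol formulation "is not inferior to 75% hypertonic glucose in terms of safety". No margin is given and no event is named.
- **Secondary endpoint – safety.** The section first casts a wide net: "Any type of adverse event (major or minor) that arises through the period of the study (D0 to D60) will be tracked". It then narrows to a named list, which opens "Adverse events that will be directly analyzed at the secondary endpoint (Additional file 3) are stains (limited to the target area), hematomas (limited to the" and closes with edema and with phlebitis of the treated limb. Pain is evaluated by questionnaire, and two blinded surgeons score hyperpigmentation from 0 to 5 on the D60 photographs. DVT is to be recorded if it occurs, and major events are to be reported.
- **Post-treatment (D7) and Post-procedure (D60).** Both visits ask about allergies, respiratory complaints, syncope, scotoma and suspected DVT, as well as edema and phlebitis. The D60 list adds ulceration: "allergies, edema, respiratory complaints, syncope, scotoma, suspected DVT, phlebitis, ulceration) will be registered".
- **Background.** Of polidocanol: "Chest pain, cough, anaphylaxis, scotoma, and gas embolization are unusual, but serious adverse events". The section adds that these are commonly related to miscalculated dosages.
- **Expected adverse effects.** Major complications with 75% glucose are said to be reported rarely, whereas "polidocanol is associated with some reports of adverse events such as gas embolism and deep venous thrombosis". Ulcers are listed as minor events related to both agents.
- **Statistical analyses.** Categorical variables are compared by chi-square or Fisher's exact test. The only power statement concerns the primary efficacy score.

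**The concern.** The hypothesis covers safety as a whole. The article itself says where the two arms might differ: several systemic events are tied to polidocanol, and 75% glucose is described as having few major complications. The named analysis set contains none of those systemic events and no ulceration.

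If the plan is followed as written, a report could find similar rates of stains, hematomas, edema and phlebitis and call the formulation not inferior in safety. The events most likely to count against it would appear only as recorded or reported items, with no stated comparison and no statement of how high a rate the data leave open. A non-significant chi-square or Fisher test would not establish non-inferiority even for the listed events.

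**Working it through.** **1. The plan's own figure.** Inputs from Statistical analyses: 48 per arm, difference 0.9, SD 1.5, alpha 0.05 (taken as two-sided, since sidedness is not stated). Standardised difference 0.9/1.5 = 0.6. Power = Φ(0.6 × √(48/2) − 1.96) = Φ(2.94 − 1.96) = 83.6%; the t-test version gives 82.9%. The stated power above 80% is reproduced, but it concerns the efficacy score only and says nothing about safety.

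**2. Collected against directly analysed.**

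| Event | On a visit list | Directly analysed | Linked in the article to |
|---|---|---|---|
| Edema, phlebitis | D7 and D60 | Yes | both agents |
| Stains | via the safety section | Yes | both agents |
| Hematomas | via the safety section | Yes | not stated |
| Allergy | D7 and D60 | No | polidocanol (anaphylaxis) |
| Respiratory complaints | D7 and D60 | No | polidocanol (cough) |
| Scotoma | D7 and D60 | No | polidocanol |
| Suspected DVT | D7 and D60 | No | polidocanol |
| Syncope | D7 and D60 | No | not stated |
| Ulceration | D60 | No | both agents |

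**3. What zero events would show.** With 0 events in n patients, the one-sided 95% upper limit is 1 − 0.05^(1/n), and the upper end of the two-sided exact interval is 1 − 0.025^(1/n).
- n = 48: 6.1% and 7.4%.
- n = 53 (106/2, the enrolment target with no losses): 5.5% and 6.7%.

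**4. Chance of seeing an event at all.** Probability of at least one event in an arm of 48 is 1 − (1 − p)^48. The article gives no rates, so these are assumed: p = 0.1% gives 4.7%, p = 1% gives 38%, and p = 2% gives 62%.

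**5. Would a comparison of rare events be informative?** With 48 per arm, Fisher's exact test gives p = 0.056 for 5 against 0 events and p = 0.026 for 6 against 0. Its power, at assumed true rates, is below 0.1% for 2% against 0%, 3.2% for 5% against 0%, and 25% for 10% against 1%.

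**6. What non-inferiority would need.** With equal true rates p, margin m, one-sided 0.025 and 80% power, n per arm = (1.960 + 0.842)² × 2p(1 − p)/m². Rates and margins are assumed.
- p = 1%, m = 2 points: 389 per arm.
- p = 2%, m = 2 points: 770 per arm.

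Solving for m with n = 48, the smallest supportable margin for a common local event is about 17 points at a 10% rate, 26 points at 30% and 29 points at 50%.

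**The case against.** The strongest defence is that the safety plan is wider than the short list. Four readings go too far and should not be drawn from the text.

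- *Safety rests on four local events alone.* It does not. Pain and the blinded hyperpigmentation score are also safety measures, all adverse events are tracked, major ones are reported, and edema carries no restriction to the target area or limb.
- *The unlisted events will never be compared.* The article does not say so. The chi-square and Fisher provision is not confined to the listed events, and Additional file 3 and any analysis plan are not shown. Reporting rare major events descriptively is ordinary practice in a trial of about 100 patients.
- *The omission is what makes the hypothesis unanswerable.* It is not the main reason. Without a margin, and with only tests of difference, the hypothesis would fail even for stains or phlebitis. Steps 5 and 6 show that listing rare events would not rescue it.
- *Ulceration, or a gap in the visit lists, is evidence against polidocanol or of missing data.* Ulcers are linked to both agents. The D7 list is illustrative, the D60 visit covers any new event, and the safety section says its data are collected at the visits. One identical checklist would be a preference, not a correction.

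The defence does not remove the mismatch. The article makes a positive choice of which events are directly analysed and sets others apart as recorded or reported. That choice stands beside a safety hypothesis with no such limit. The remark about miscalculated dosages may lower the expected rate of systemic events, but it does not make a claim covering them testable.

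**Conclusion.** The point holds in this form: the article hypothesises non-inferiority on safety overall, while its directly analysed adverse events omit the systemic events and ulceration that it collects. An unqualified conclusion of non-inferiority would not be supported, for three reasons together: no margin or defining safety endpoint, only tests of difference, and about 48 patients per arm. An arm with no events of a given type would still be compatible with a rate of up to 6.1% (one-sided 95%), or 5.5% if all 53 per arm were followed.

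The zero-event limits rest only on the sample size. The detection probabilities, Fisher power and non-inferiority sample sizes rest on assumed rates and margins, because the article gives none. The consequence is a limit on what the trial may conclude about safety; the efficacy comparison is unaffected.

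**What to change.** 1. In Secondary endpoint – safety, add allergy, respiratory complaints, syncope, scotoma, suspected or confirmed DVT, and ulceration to the events summarised by arm. Give the proportion of patients with any systemic event and with any adverse event, with exact 95% confidence intervals for each arm and for the difference.
2. In Hypothesis, replace the overall non-inferiority claim with a descriptive safety comparison. Make no non-inferiority or equivalence claim for systemic events. Make none for local events either, unless an endpoint and a margin are specified in advance and judged by a confidence interval; step 6 shows how wide that margin would have to be at this sample size.

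The cost is some rewording and a few extra tables from data already collected. The downside is a narrower safety claim.
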